### **13.2 Criteria for Study Endpoint Evaluability**

Our assessment of the outcomes will be guided by intention-to-treat (ITT) principles, with all patients analyzed in their randomized groups, irrespective of actual treatment received or

[figure not shown]

number of study assessments completed. All randomized patients will have baseline outcome data and be evaluable for the comparative effectiveness analyses.

## 14.0 BIOSTATISTICS

This study is a two-arm, parallel group, randomized clinical trial (RCT) to compare the effectiveness of MT versus CBT for anxiety and co-morbid symptoms in a diverse, heterogeneous sample of 300 cancer survivors. Participants will be randomized in a 1:1 ratio (MT: CBT) using randomly permuted blocks of random length, stratified by current anxiety medication use (yes/no), preferred language (English/Spanish), and study site (MSK/MCI) (see Section 7.2). We plan to enroll 300 survivors over a two-year period.

### 14.1 Populations for Analyses

Consistent with ITT principles, all patients will be analyzed in their randomized groups, irrespective of actual treatment received or number of study assessments completed. All randomized patients will have at least the baseline outcome assessment and will be included in the comparative effectiveness analyses.

### 14.2 Statistical Analyses.

We describe the analysis for each aim below using the intention-to-treat (ITT) principle (i.e. participants will be analyzed according to their randomly assigned treatment group regardless of drop-out or treatment adherence status). For all specific aims, our main analytic tool will be linear mixed-effects models (LMMs) because our primary outcome (anxiety) and secondary outcomes (e.g. fatigue, insomnia) are repeated continuous outcomes over time. This statistical procedure takes into account within-subject correlations from repeated measurements in the same subjects and allows estimation of between-group differences without necessitating exclusion of participants with missing data. The general template of each LMM will model the outcome as a function of treatment arm and assessment time (categorical), controlling for the randomization stratification variables (baseline anxiety medication use, preferred language, study site), and including a subject-specific random intercept. We will tailor this general LMM template to test the specific aim hypotheses by adding interaction terms (e.g. time-by-intervention) and additional covariates of interest to the model, and by reparametrizing the assessment time variable to focus on specific contrasts.

**Aim 1 – Hypotheses 1(a) and 1(b):** We will plot the outcome measure trajectories by randomization arm over time and summarize each outcome measure at each assessment time by treatment arm using descriptive statistics. Comparisons between randomization arms with respect to changes in symptom outcomes will be based on specific coefficients from time-by-arm interactions added to the general LMM template described above. Specifically, the model will include all time points (categorical) at which the outcome was assessed (baseline, week 4, 8, 16, 26), and the time-by-arm interaction will include multiple coefficients corresponding to the time-by-arm interaction at each discrete post-baseline time point. Our

[figure not shown]

statistical inferences, however, will focus on the interaction coefficients at 8 and 26 weeks, which are interpreted as the differences between arms in change from baseline to 8 and 26 weeks, respectively. For Hypothesis 1(a), our two primary endpoints are HADS anxiety score changes at 8 weeks and 26 weeks. Based on the LMM coefficients for the time-by-arm interaction at week 8 and week 26, we will perform two tests of whether MT is non-inferior to CBT at reducing HADS Anxiety within a non-inferiority margin of 0.35 SD for both comparisons. Non-inferiority of MT to CBT will be tested at significance threshold of  $p < 0.025$  for each comparison, controlling the overall Type I error at 0.05 for our primary endpoint comparisons. For Hypothesis 1(b), we will use a similar LMM evaluating BFI scores over time to test whether the MT arm had significantly greater improvement in fatigue (BFI score) compared to the CBT arm at weeks 8 and 26. In contrast to our primary endpoint non-inferiority comparisons, these tests will be superiority tests. For the other co-morbid symptoms (e.g. depression, insomnia) and quality of life, we will compare the arms using the same methods described for Hypothesis 1(b). Given that a small number of cancer survivors may experience recurrence of disease during the 26-week study, we will conduct sensitivity analyses, excluding those individuals who experienced a recurrence during the study period. Our sensitivity analyses will not replace the primary analysis.

**Aim 2 – Heterogeneity of Treatment Effect (HTE):** An essential part of patient-centered care is recognizing that not all patients will respond to treatments the same way. We will conduct exploratory, hypothesis-generating HTE analyses to identify patient-level factors associated with treatment response to either MT or CBT by incorporating six relevant variables (i.e. sex, race, ethnicity, education, outcome expectancy, and time since cancer diagnosis) and variable-by-intervention interaction terms in our mixed-effects model described above. For these five exploratory LMM-based analyses, we will guard against inflated Type I error due to multiple testing by adjusting the variable-by-intervention interaction p-values for the false discovery rate. We recognize that this type of subgroup analysis, although patient-centered, may need to be interpreted with caution and cannot replace the primary analyses. We intend to approach the evaluation of HTE based on existing literature and patient/clinician input. Our current focus on evaluating and reporting HTE will be based on the approach proposed by Kent et al. However, recognizing other factors may also contribute to treatment responses, we will apply promising emerging Bayesian and machine learning methods, which can identify HTE and subgroups based on multiple variables simultaneously and are potentially more powerful than traditional univariate methods.

**Qualitative Analyses:** All interviews will be transcribed verbatim and imported into NVivo Pro version 12.0 for analysis. The semi-structured interviews will be analyzed using theoretical thematic analysis procedures per guidelines by Braun and Clarke. Such analysis is aimed at identifying patterns driven by an *a priori* theoretical framework or research questions. Themes will be identified using a semantic approach in which themes are derived from “the explicit meaning of the data and the analyst is not looking for anything beyond what a participant has said.” Two coders will independently code each interview

[figure not shown]

transcript. Coding discrepancies will be resolved through discussion until consensus is reached. The codes will then be organized into categories, reviewed, and subsequently organized into broader themes. Interviews from each treatment arm will be analyzed separately, and then compared for convergence and divergence. The themes will be linked to PROs to explore whether specific themes may vary by the magnitude of change in the HADS anxiety score. To augment the HTE analyses, we will also explore whether qualitative themes differed by subgroups (e.g. sex, race, ethnicity, education, high/low expectation) within each treatment group. We will include patient co-investigators during data analyses and interpretation to better understand what types of patient experiences may be unique to MT or CBT. This patient-centered perspective will be critical during the dissemination of study findings to patients and clinicians.

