**4.2.a. Music Therapy.** The MT protocol (Appendix A) is based on the neuroscience of music, the social-cognitive processing model, the scientific literature on MT, and our own clinical and research experience. Healthy psychological adjustment during cancer survivorship requires the processing of feelings and thoughts related to one's cancer journey in a supportive context. Therefore, we have structured the intervention protocol to gradually build patient-therapist rapport and allow for greater emotional expressivity and deeper cognitive processing. Guided by the social-cognitive processing model, the first few sessions will focus on building a trusting relationship with the therapist, whereas later sessions will focus on cognitive processing of cancer-related experiences and current fears, worries and hopes, using playlist creation and songwriting as an outlet for reflection, expression, and meaning-making. Research also suggests that patients prefer receptive modes of engagement during initial exposure to music therapy. As such, the early sessions will focus on receptive techniques (e.g. music-guided stress management) and later sessions will progress to more active music therapy techniques (e.g. songwriting). The protocol includes homework activities in between sessions to promote self-management skills (e.g. use of music-guided deep breathing), strengthen social connections (e.g. sharing of meaningful song with loved ones), provide outlets for cognitive processing (e.g. composing song lyrics), and serve as transitions to the subsequent sessions. Patients will receive a workbook with materials for each session (Appendix H). The MT interventionists will be board-certified music therapists.

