**4.2.b. Cognitive Behavioral Therapy.** The CBT protocol (Appendix B) is based on the scientific literature, as well as our clinical and research experience. CBT therapists will include psychologists, social workers, and trainees in clinical psychology doctoral programs and Masters-level social work programs, as reflective of real-world practice and implementation of CBT in oncology settings. In addition to psychologists, we included social workers as CBT interventionists because they are the most commonly employed mental health providers in cancer care. To expand the pool of eligible therapists and enhance future intervention dissemination, the social workers administering CBT will not be required to have prior CBT training or experience in oncology care. Informed by the cognitive behavior model of anxiety, CBT focuses on the relationship between thoughts, behaviors, and emotions and how thoughts and behaviors can exacerbate or reduce anxiety. The protocol consists of psycho-education on anxiety, relaxation techniques, and cognitive restructuring, and strategies for planning activity engagement and managing realistic worries. These components target the somatic symptoms of anxiety (e.g. muscle tension), as well as the thoughts (e.g. "What if my next scan is bad?") and behaviors (e.g. excessive symptom monitoring) that trigger and exacerbate anxiety. Once identified, these problematic thoughts and behaviors are replaced with thoughts and behaviors that prevent and reduce anxiety. Each session will follow a consistent format that includes an overview of session content, review of the homework exercise from the prior session, information on a new skill for managing anxiety, discussion of the upcoming homework exercise, and a plan for completing the exercise before the next session. Patients will receive a workbook with materials for each session (Appendix I).

[figure not shown]

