however, we present our power calculation based on two-sample t-tests of differences between the arms in their change scores. Therefore, our power estimate is conservative; that is, in our LMM-based analysis, we will have slightly higher power than presented below, with all other assumptions held constant. Assuming 150 participants are randomized to each arm, 15% attrition, and a one-sided significance threshold of 0.025 (controlling the overall Type I error at 0.05 for our two primary endpoint comparisons), we will have 80% power to find MT non-inferior to CBT with respect to week 8 and 26 HADS Anxiety scores within a non-inferiority margin of  $D=0.35$  SD. Justification of Non-inferiority Margin: A recent large study used multiple rigorous methods to empirically estimate a difference of 1.7 points as the MCID for the HADS scales. In preliminary data of CBT recipients with baseline HADS Anxiety scores  $\geq 8$ , the SD for the HADS Anxiety score was 4.2 at week 8 (end of treatment). Additionally, in a large, recently completed acupuncture trial of cancer survivors, among 159 patients with baseline HADS Anxiety scores  $\geq 8$ , the HADS Anxiety score SD was 4.0 during follow-up. Based on these studies, we assume our HADS Anxiety score SD will be approximately 4.2. Dividing the raw-score MCID of 1.7 points by 4.2 yields standardized difference (i.e. Cohen's D) of 0.40. Our non-inferiority margin of  $D=0.35$  SD is smaller than the HADS Anxiety standardized MCID ( $D=0.40$ ); as such, our non-inferiority margin and statistical approach will find MT to be non-inferior to CBT only if MT is not meaningfully worse than CBT. We confirmed with our patient advisory groups, using concrete examples, that the non-inferiority margin of  $D=0.35$  SD would not represent a meaningful difference between the treatments. Qualitative Analyses: The number of participants required to draw meaningful conclusions from semi-structured interviews is determined by saturation, i.e. the point at which existing themes are fully understood and no new themes emerge through further data collection. Prior research has indicated that thematic saturation can typically be obtained with fewer than 15 interview participants, although these findings were based on relatively homogenous samples. Given that we are seeking to capture perspectives from a diverse group of survivors, we will plan for 30 interviews in each treatment arm to achieve thematic saturation. We achieved saturation at  $N=30$  interviews in an ongoing qualitative study of our virtual integrative medicine program.

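### Therapists appear to be nested within arm, but the primary model and the 80% power treat patients as independent; if therapists differ, the non-inferiority tests run above 2.5%

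*Protocol*

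**What the plan says.** **Delivery.** Protocol section 4.2 gives each patient seven weekly 60-minute sessions. On who delivers them, section 4.2.a states "The MT interventionists will be board-certified music therapists", and section 4.2.b states "CBT therapists will include psychologists, social workers, and trainees in clinical psychology doctoral programs and Masters-level social work programs". Section 4.2.b adds that social workers giving CBT need no earlier CBT training. Under section 4.2.c a therapist who joins later is trained by the Lead Therapist for their own treatment.

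**Primary model.** Section 14.2 specifies a linear mixed model with arm, categorical time, the time-by-arm interaction, the three stratification variables (medication, language, site) and one random effect, an intercept per subject. The model "takes into account within-subject correlations from repeated measurements in the same subjects". Inference rests on the week 8 and week 26 interaction coefficients, each tested against a "non-inferiority margin of 0.35 SD for both comparisons".

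**Power.** The 80% figure comes from "two-sample t-tests of differences between the arms in their change scores" and is called conservative. Its inputs are "Assuming 150 participants are randomized to each arm, 15% attrition" and a one-sided 0.025 per test.

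**Sensitivity analyses.** Those named concern recurrence, progression or death, and missing data. No therapist effect, ICC, design effect or therapist count appears.

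**The concern.** Patients treated by the same therapist may have correlated outcomes. If each therapist works in one arm only, differences between therapists do not cancel in the MT-CBT comparison; they add to its variance. A therapist effect starts when treatment starts, so it enters the baseline-to-week-8 and baseline-to-week-26 changes, which are exactly what is tested. The subject intercept absorbs only what is constant for a patient over all visits, and site does not separate therapists within an arm.

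A standard error that omits this variance is too small. In a non-inferiority trial the resulting error runs toward the favourable claim, because an interval that is too narrow clears the margin too often. Section 13.1 counts success at either time point, and its overall 0.05 is the sum of two tests that must each hold 0.025. If each test exceeds 0.025, that guarantee is lost.

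**Working it through.** **Inputs from the protocol (section 14.2).** Margin 0.35 SD; one-sided alpha 0.025 (critical value 1.96); 150 per arm with 15% attrition, so 150 × 0.85 = 127.5 per arm; stated power 80%; true difference zero for power. The 4.2-point SD is 1 on this scale.

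**Assumed, because the protocol does not give them.** Therapists per arm (k) and the therapist ICC of the change score. Caseloads are taken as equal.

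**Step 1: the stated power.** 0.35 × √(127.5/2) = 2.795, and Φ(2.795 − 1.96) = Φ(0.835) = 79.8%. The plan's 80% reproduces, and it does so with independent patients, that is, with ICC = 0.

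**Step 2: clustering.** With m = 127.5/k patients per therapist, the design effect is DE = 1 + (m − 1) × ICC. Then:

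- error of the planned test: 1 − Φ(1.96/√DE)
- power of the planned test: Φ((2.795 − 1.96)/√DE)
- power of a test with the correct standard error: Φ(2.795/√DE − 1.96)
- the same with a t reference: noncentral t on 2(k − 1) df with noncentrality 2.795/√DE
- interval width relative to plan: √DE, or √DE × t/1.96 with the t critical value (2.048, 2.145 and 2.306 for k = 15, 8 and 5)

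Example with k = 8 and ICC 0.05: m = 15.9; DE = 1 + 14.94 × 0.05 = 1.75; √DE = 1.322. Planned-test error is 1 − Φ(1.483) = 6.9%; planned-test power is Φ(0.631) = 74%; corrected-test power is Φ(2.114 − 1.96) = 56%.

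| k per arm | ICC | m | DE | Planned test: error | Planned test: power | Corrected test: power, normal | Corrected test: power, t | Interval wider, normal / t |
|---|---|---|---|---|---|---|---|---|
| any | 0 | – | 1.00 | 2.5% | 80% | 80% | – | – |
| 15 | 0.01 | 8.5 | 1.07 | 2.9% | 79% | 77% | 74% | 4% / 8% |
| 8 | 0.02 | 15.9 | 1.30 | 4.3% | 77% | 69% | 63% | 14% / 25% |
| 8 | 0.05 | 15.9 | 1.75 | 6.9% | 74% | 56% | 50% | 32% / 45% |
| 5 | 0.05 | 25.5 | 2.23 | 9.4% | 71% | 47% | 38% | 49% / 75% |

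The planned and corrected columns describe two different analyses and should not be read as one.

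**Step 3: does the subject intercept absorb the effect?** The random-intercept model was simulated with five visits, complete data, 127 per arm, a true difference at the margin, a therapist effect after baseline only, an assumed subject variance share of 0.5 and 4,000 runs. Rejection at the nominal 2.5% was about 2.3% at ICC 0. At ICC 0.02 it was 4.0%, 5.1% and 6.3% with 10, 6 and 4 therapists per arm; at ICC 0.05 it was 6.8%, 8.7% and 11.1%. The formula gives 3.9%, 4.9% and 6.2%, then 6.0%, 8.4% and 11.0%. The subject intercept does not remove the problem.

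**The case against.** **The nesting is inferred.** No sentence says that a therapist serves one arm only or that a patient keeps one therapist throughout. Section 7.0 lets staff of more than one institution deliver sessions, and section 4.2.c allows therapists to join during the trial. This stands as a caution. The inference is still sound, given separate professions per arm, separate Lead Therapists and an MT protocol built on rapport with the therapist (section 4.2.a).

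**Therapist differences may be small.** Section 4.2.c provides protocol training, continuing supervision, review of recordings and retraining when fidelity falls below 80%; section 16.0 requires certification before treatment. This supports the low end of the ICC range. It does not establish an ICC of exactly zero, which the plan needs. Week 26 also falls months after therapy, so its ICC need not equal that at week 8.

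**It could be left to the SAP.** The model is called a general template, and an SAP may exist. But the protocol itself fixes the random-effects structure and the basis for power.

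**Random therapists are a choice.** Treating therapists as random is partly a decision to generalise beyond those in the study. That is true, but the stated aim is to guide treatment choice in practice, and section 4.2.b picks CBT providers to mirror real-world delivery.

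**Stronger readings to avoid.** A reader might infer that false non-inferiority is shown to exceed 2.5%. The protocol gives no ICC, so the excess is conditional on one above zero. A reader might also infer that the planned test has only 47% power. That figure belongs to the corrected test in the severest case shown; the planned test has about 71% there.

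**Conclusion.** The point holds conditionally. Its direction is certain for any positive therapist ICC when therapists work within one arm and treat more than one patient: the standard errors at weeks 8 and 26 are too small and each test exceeds its one-sided 2.5%. The size is not known. Across the assumed scenarios the excess runs from slight (2.9%) to serious (9.4%). The planned test's power is about 79% to 71%. A valid clustered test has about 77% to 47% power by normal approximation, or 74% to 38% with 2(k − 1) df. These ranges rest on assumed therapist numbers, ICCs and equal caseloads, with one ICC applied to both time points. Calling the stated power conservative is not supported once clustering is allowed for.

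**What to change.** 1. Record the treating therapist for each patient, by session if the therapist can change.
2. Pre-specify in the primary model a therapist random effect, nested in arm and acting at post-baseline visits. A therapist intercept that is constant over all visits, baseline included, would cancel from the change and correct nothing.
3. Use Satterthwaite or Kenward-Roger degrees of freedom. Allow arm-specific therapist variances only if there are enough therapists to estimate them.
4. Remove the description of the power as conservative, and restate power for the planned number of therapists over an assumed ICC range such as 0.01 to 0.05.

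**Cost.** One data field, which session scheduling should already supply, and one model term. No additional patients or study procedures are needed to make the change. The real price is precision: intervals about 4% wider in the mild case and about 50% wider in the severe case, more with small-sample degrees of freedom, and a less favourable stated power. Few therapists per arm would also make the therapist variance itself imprecise. The change should be fixed before treatment allocation is unblinded.

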## **7.2 Randomization**

Patients will be randomized using MSK's Clinical Research Database (CRDB), a secure computer system that ensures full allocation concealment. After eligibility is established and consent is obtained, patients will be registered through the Clinical Trials Management System (CTMS) and then randomized using the Randomization Module in the CRDB. Randomization will be 1:1 (MT: CBT) using randomly permuted blocks of random length, stratified by current anxiety medication use (yes/no), preferred language (English/Spanish), and study site (MSK/MCI). The PI and biostatisticians will be blinded to treatment allocation.

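### As written in 14.2, the stratification variables contribute essentially nothing to the week-8 and week-26 change contrasts; adding stratum-by-time terms makes the stated adjustment reach them, at almost no cost and for a small gain

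*Protocol*

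**What the plan says.** Protocol 7.2 has allocation "stratified by current anxiety medication use (yes/no), preferred language (English/Spanish), and study site (MSK/MCI"), and 14.0 repeats the same three factors. The general template in 14.2 regresses the outcome on arm and categorical time, "controlling for the randomization stratification variables (baseline anxiety medication use, preferred language, study site), and including a subject-specific random intercept".

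For Aim 1, 14.2 says that "the model will include all time points (categorical) at which the outcome was assessed (baseline, week 4, 8, 16, 26"), so week 0 is a response and not a covariate. No constraint is placed on the arm means at week 0. Arm comparisons are "based on specific coefficients from time-by-arm interactions added to the general LMM template described above". Inference rests on the week-8 and week-26 coefficients, "interpreted as the differences between arms in change from baseline to 8 and 26 weeks". The template may be tailored "by adding interaction terms (e.g. time-by-intervention) and additional covariates of interest to the model", but no term combining a stratification variable with time is named. Hypothesis 1(b) and the other symptom outcomes follow the same method.

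**The concern.** Having stratified the randomisation, the plan says that the model controls for the stratification factors. On the natural reading they enter as main effects, each with one coefficient common to all visits. Such a term describes differences in level between, say, patients on and off anxiety medication. The primary tests do not use levels. They use change from week 0, from which a constant shift is removed.

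The plan therefore states an adjustment that does not reach the tests it is meant to serve. If patients on medication, Spanish speakers or patients at one site improve by a different amount, that variation stays in the error term although the arms are balanced on it by design. At stake is a little precision in the two non-inferiority tests and in every secondary comparison built on the template.

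**Working it through.** **Inputs from the Protocol (14.0, 14.2).** 150 per arm, 1:1; 15% attrition, so 127.5 evaluable per arm; margin 0.35 SD; SD 4.2, so the margin is 0.35 × 4.2 = 1.47 points; one-sided 0.025 per test; stated power 80%, from two-sample t-tests on change scores; five response times; three two-level stratification factors.

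**Step 1: reproduce the stated power.** Power = Φ(0.35 × √(127.5/2) − 1.96) = Φ(2.794 − 1.96) = 0.798 (0.795 with the noncentral t). This matches 80%. The calculation contains no covariate adjustment.

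**Step 2: why the main effects drop out.** Let z be a patient's stratification variables and γ their visit-constant effects. With complete data and a free mean for each arm at each visit, the fitted mean for arm a at visit t is

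m(a,t) = ȳ(a,t) − z̄(a)′γ̂.

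The correction z̄(a)′γ̂ is the same at every visit, so

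m(a,8) − m(a,0) = ȳ(a,8) − ȳ(a,0),

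and likewise for week 26. The arm difference in change is the raw one, whatever γ̂ is. In the random-intercept model its standard error depends on the within-patient variance, which a time-constant covariate does not alter. A generalised least squares check with exchangeable and with AR(1) covariance also gave identical week-8 estimates and standard errors with and without the factors.

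**Step 3: numerical check, complete data.** REML random-intercept fits, 400 simulated trials of 300 patients per scenario. Assumptions not in the documents: within-patient correlation 0.5; factor prevalences 0.40, 0.20 and 1/6; factor effects on level of 1.5, 1 and 1 points; effects on change either zero or the same sizes. Adding the main effects moved the estimates by at most about 1e-13 points and the standard errors by about 1e-8. A fit of one data set in standard software gave −0.53917 (week 8) and −0.06646 (week 26), each with SE 0.49564, both with and without the factors.

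**Step 4: 15% attrition (assumed monotone and completely at random).** The cancellation is no longer exact, because patients with missing visits bring some between-patient information into the contrast. The estimates move by an SD of 0.013 to 0.026 points (largest 0.11 in 400 trials) against an SE of about 0.5. The SE moves by at most 0.0014, and 0.0014/0.518 = 0.27%. At 30% attrition the SD is 0.018 to 0.035 points and the SE moves by about 0.5% at most.

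**Step 5: what stratum-by-time terms add.** Mean SE of the week-26 contrast at 15% attrition:

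| Factors affect | No factors | Main effects, as written | Stratum-by-time |
|---|---|---|---|
| Level only | 0.5125 | 0.5124 | 0.5127 |
| Level and change | 0.5178 | 0.5173 | 0.5129 |

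Power = Φ(1.47/SE − 1.96). In the second row this gives 81.0%, 81.1% and 81.8%. The SE falls by 1 − 0.5129/0.5173 = 0.9%. The one-sided error of the model as written would then be roughly 1 − Φ(1.96 × 0.5173/0.5129) = 1 − Φ(1.977) = 2.4%, against the nominal 2.5%. In the first row there is no gain.

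The size of the gain depends on the assumed effects. One complete simulated data set with larger effects on change (2, −1.5 and 1 points) took the SE from 0.4218 to 0.4084, about 3% lower. The Protocol gives no figure for how strongly these factors predict change.

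**The case against.** The strongest reply is that this is a matter of parameterisation. The template can be tailored with further interactions, its wording does not literally say main effects only, and such detail is often left to an analysis plan that is not shown. The consequence is also tiny: no bias, error at or below nominal, and a power figure that never relied on the adjustment.

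The second half stands and sets the size of the point. The first half stands only in part. The Protocol itself fixes the responses, the adjustment variables, the Aim 1 interaction and the two coefficients tested. The tailoring clause offers time-by-intervention as its example, and the Aim 1 paragraph then specifies the model without any stratum-by-time term. An analyst following the text would fit the model examined here.

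Three stronger readings are tempting and not supported:

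- **That the adjustment has no effect at all.** This is exact only with complete data. The plan expects 15% attrition and keeps incomplete patients in the model, so the factors then enter weakly.
- **That the primary tests are invalid or materially underpowered.** Nothing here biases the contrast or inflates the error, and the 80% reproduces without any adjustment.
- **That the cancellation occurs however baseline is handled.** It depends on leaving the week-0 means unconstrained. With a common baseline mean for both arms, adding the factors as main effects did move the week-8 estimate, for example from −0.560 to −0.577 in one simulated data set and from −0.185 to −0.230 in another.

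**Conclusion.** The point holds in a limited form. Under the natural reading of 14.2, controlling for the stratification variables contributes exactly nothing to the primary change contrasts with complete data, and changes their standard error by under 0.3% at the planned attrition. The cost is slight conservatism if medication use, language or site predicts change, and nothing if they predict level only. On the assumed effects the loss is about 1% in standard error and 0.7 of a power point. That rests on assumed effect sizes, prevalences, correlation and random dropout, none of which the Protocol supplies. It is worth correcting because the plan claims an adjustment that its primary tests do not receive and the correction is almost free; no conclusion of the trial is likely to turn on it.

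**What to change.** In 14.2, state that each stratification variable and its interaction with categorical time are included in the primary mixed model and in those for the secondary outcomes. The week-8 and week-26 time-by-arm coefficients keep their meaning as arm differences in change from baseline. This adds 3 factors × 4 post-baseline visits = 12 nuisance parameters in 300 patients, uses data already collected and needs no extra participants.

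An alternative model would also serve: constrain the baseline mean to be common to both arms, or model the post-baseline scores with the baseline score as a covariate, in either case together with the stratification variables. These are different models with different coefficients, so the choice should be stated explicitly. Modelling post-baseline scores with baseline in no role at all would not do, because it would no longer estimate change from baseline.

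Whichever form is chosen should be fixed before unblinding, so that it cannot be seen as a later change to a non-inferiority test.
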